## **12. QUALITY ASSURANCE AND CONTROL**

### **12.1 Data handling and record keeping / archiving**

All study-related information will be stored securely at research department of the Reha Rheinfelden. Participant information will be stored in locked file cabinets in areas with limited access. All reports, data collection, process, and administrative forms will be identified by a coded ID number only to maintain participant confidentiality. All records that contain names or other personal identifiers, such as locator forms and informed consent forms, will be stored separately from study records identified by code number. All local databases will be secured with password-protected access systems. Forms, appointment books, and any other listings that link participant ID numbers to other identifying information will be stored in a separate, locked file in an area with limited access.

#### **12.1.1 Case Report Forms**

Questionnaires will be filled in by patients. The final scores (i.e. VAS and ODI score) will be recorded to the paper-CRF (p-CRF) by the PL or a study assistant. Secondary outcomes, i.e. motion tracking data and platform oscillation, will be recorded electronically. The calculated outcomes for postural control (i.e. averaged joint angle and UCM-Index) will be transferred to the p-CRF by the PL and a study assistant (double data entry).

#### **12.1.2 Specification of source documents**

Questionnaires scores will be transferred from the paper questionnaires (VAS and ODI) which will be filled in by the patients.

Dose and frequency (i.e. compliance) will be derived from the paper exercise diary filled in by the patients.

Therapy documentation for the conventional therapy is recorded on a pre-defined documentation sheet designed to record mode and usage of additional devices.

#### **12.1.3 Record keeping / archiving**

All study data will be archived for 10 years after study termination or premature termination of the clinical trial. All digital data is archived on the clinic's server and backed up daily. Video-data is stored on external hard-drives to spare server capacities. Paper data is archived in the research department's office, which is not accessible to the public.

## **12.2 Data management**

All study related patient data will be entered directly into the digitalised and anonymised case report forms. Results from the written questionnaires will be transferred immediately. Recorded joint configurations are stored as raw data to compute the UCM and CM in a separate step.

Therapy documentation and training protocols will be transferred to an anonymised log-book using study identification numbers for recognition. No personal data, that could identify the patients, will be stored for study purposes or used for analyses.

#### **12.2.1 Data Management System**

A VMWare Horizon environment is maintained in the clinic which is accessed via the local thin client. It runs Windows 7 platform and provides the MS Office package needed for the report. However, statistical and motion tracking software is not installed on the clinic's server and must be operated with an external notebook provided by the ETH Zurich. All raw data is recorded straight to the notebook and backed up on the server (only anonymised motion tracking data, i.e. angular variation and postural information). Video files are stored on the Notebook and the external hard drive, but not on the Server.

Data structures will be organised using Matlab (MATLAB 2014a., The MathWorks Inc.: Natick, Massachusetts).

#### **12.2.2 Data security, access and back-up**

The digital data is backed up daily on the clinic's server (except Video files, these are backed up on a second external hard drive once a month).

#### **12.2.3 Analysis and archiving**

A data structure in Matlab will contain an array for each patient (ID.01 to ID.20). Each array will contain vector information of the assessed outcomes. In a second step, a technical assistant, not involved in the study, will allocate a new identification number to each participant and separate the control from the experimental group. This new data sheet will then be handed back to the PL who will conduct final analysis. This method reduces the risk of bias as the PL remains blinded to each individual's group allocation during statistical analysis. Specifically, at the end of the study, the folder containing ID01 to ID20 data is edited by the technical assistant to re-randomise all ID numbers and transform these to any number between 87300 and 87390 with either an A or B as suffix, depending on the group, e.g. 87345\_A. The PL will not know whether A or B is the experimental group until analysis is completed.

Study related original patient documents will be archived for 10 years on an external hard-drive. After that period patient documents will be destroyed in accordance with the clinic's data destruction guidelines.

Non-numeric data is entered onto excel sheets and coded. The coded lists are also exported to Matlab and allocated to the patient within the data structure.

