| Number of Participants with Rationale: | 20 to 30 patients with low back pain (min. 10 per arm) and 20 healthy controls for the normative data. Based on previous studies with similar endpoints, the selected amount of participants has shown to suffice for an explorative approach with a desired power of 80% and an alpha of 0.05. |
| Study Duration:                        | September 2014 to December 2015                                                                                                                                                                                                                                                                 |
| Study Schedule:                        | Begin recruiting: January 2015
Last assessment: December 2015                                                                                                                                                                                                                                |
| Investigator and project leader:       | [name]
[contact]
[contact]                                                                                                                                                                                   |
| Study Centre:                          | Reha Rheinfelden
[name]

[name]                                                                                                                                                                                                                                   |
| Statistical Considerations:            | Student T-Test will be applied for group comparison at Baseline for cross-sectional comparison of LBP group with healthy group.

Repeated measure ANOVA with post-hoc analysis will be applied to test therapy effects.

Effect size will be calculated with Guyatt's effect size.  |
| GCP Statement:                         | This study will be conducted in compliance with the protocol, the current version of the Declaration of Helsinki, the ICH-GCP or ISO EN 14155 (as far as applicable) as well as all national legal and regulatory requirements.                                                                 |

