### 11.2 Determination of Sample Size

This is the first study of its kind to investigate the effects of a sensorimotor training on dynamic postural control in patients with CNLBP and is therefore of explorative nature. Related to the primary hypothesis, however, a study using the same outcomes investigated the effects of treadmill training on gait in down-syndrome children and compared them to healthy subjects [29]. Although this is not a comparable study population it was used to estimate the power of the test. With a mean between-group difference of 1.4 and a pooled standard deviation of 0.19 the study revealed highly significant group effects ( $N=15$ ,  $p<0.01$ ).

Several studies have investigated the effects of sensorimotor training on pain and functional status. Two of the most recent ones [30, 31] have found significant time and group interactions using the same outcomes. Applying the results of these studies to a sample size calculation with an alpha value of 5% and the desired power 80%, it is expected that 10 patients per arm would suffice to reveal group differences and to detect change.

In terms of the secondary hypothesis, it must be referred to an article which used a similar motor task in an experimental setup with cross-sectional analysis of healthy participants. For the detection of within-subject difference of control parameters of the uncontrolled manifold approach, Scholz et al. [27] found that with a deflection of 0.06 m, the projections of joint configurations to the manifold differed significantly to the projection in the range space ( $N=9$ ,  $F_{1,8}=25.8$ ,  $p<0.001$ ). With a mean difference of 0.055 and a standard deviation of 0.015, this calculates to a power of  $>0.9$ .

Considering these findings and taking into account the explorative approach of this trial, a total number of 30 participants is planned (10 healthy subjects and 10 patients per intervention arm).

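### The only coding step masks treatment arm for ID01 to ID20, so the patient-versus-healthy comparison is derived and analysed with no masking of who is a patient

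*Protocol*

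**What the plan says.** Protocol section 12.2.3 describes the one coding step in the plan. It starts from "A data structure in Matlab will contain an array for each patient (ID.01 to ID.20". A technical assistant who is otherwise uninvolved "will allocate a new identification number to each participant and separate the control from the experimental group". In detail, the assistant takes the ID01 to ID20 folder and is to "transform these to any number between 87300 and 87390 with either an A or B as suffix, depending on the group". The section states the purpose: "This method reduces the risk of bias as the PL remains blinded to each individual's group allocation during statistical analysis". It also states what stays hidden: "The PL will not know whether A or B is the experimental group until analysis is completed".

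The other blinding text (sections 6.1, 6.2.2, 6.3, 7.3 and 11.4.2) likewise concerns experimental versus control allocation only.

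Section 11.1 sets three hypotheses. The second (postural variability) and the third (cervical proprioception) compare patients with healthy controls, and section 11.4 tests them with independent t-tests. The synopsis lists this comparison as one of two main objectives.

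On numbers, section 11.2 says "a total number of 30 participants is planned (10 healthy subjects and 10 patients per intervention arm", while the synopsis says "20 to 30 patients with low back pain (min. 10 per arm) and 20 healthy controls for the normative data".

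On processing, section 12.2 says: "Recorded joint configurations are stored as raw data to compute the UCM and CM in a separate step".

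**The concern.** The protocol accepts that an analyst's knowledge of group is a source of bias and takes trouble to remove it, but only for the comparison of arms. For the comparison with healthy controls it removes nothing. If any step between the stored recording and the analysed value leaves room for discretion, including which values to exclude, a lean in one direction goes straight into the group difference. It could not afterwards be told apart from a real deficit in the patients. Section 13 plans a publication on the cross-sectional findings, so the comparison will be read in its own right.

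**Working it through.** **1. Who the coding step covers.** Section 11.2 plans 2 arms × 10 patients = 20, which reproduces ID01 to ID20 exactly. No ID is left for a healthy participant.
- Under section 11.2 the scheme covers 20 of 20 + 10 = 30 participants.
- Under the synopsis it covers 20 of 20 + 20 = 40, up to 20 of 30 + 20 = 50.
- With 30 patients, numbers 21 to 30 would also fall outside the arm masking as written.

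Section 12.2.3 speaks of renumbering every participant, but this does not widen the scheme, because the detail that follows confines it to ID01 to ID20 and to two suffixes. Both suffixes denote patients, so a record that carries either one is identified as a patient's.

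**2. Whether status is otherwise hidden.**
- Section 7.2: the project leader contacts referred patients and is the contact for interested participants.
- Section 12.1.1: the project leader or a study assistant records the VAS and ODI scores.
- Synopsis: healthy participants must score 0 on both scales, and patients must score above 0 on both. The scores therefore separate the groups completely.
- Sections 11.4.2 and 12.2.3: the project leader does the analysis. No readable section gives the cross-sectional tests to anyone else.

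**3. Whether masking is possible.** Status cannot be hidden when the recording is made. Section 12.2, however, stores joint configurations and computes the UCM values in a separate step, so that step can be masked. The existing recoding comes too late for this: in section 12.2.3 it is a second step, applied to arrays that already hold the outcomes.

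**4. Illustration of size.** The documents give no bias figure. The shifts below are assumptions, with no true group difference and a two-sided 5% t-test.
- Non-centrality = shift / √(1/n₁ + 1/n₂), with n₁ + n₂ − 2 degrees of freedom.
- For 20 v 20: √(1/20 + 1/20) = 0.316, so a shift of 0.2 SD gives 0.2/0.316 = 0.63, and 0.5 SD gives 1.58.
- The rejection probability is the area of the non-central t beyond the two critical values.

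| Assumed shift (SD) | 20 v 10 (section 11.2) | 20 v 20 (synopsis, low) | 30 v 20 (synopsis, high) |
|---|---|---|---|
| 0 | 5.0% | 5.0% | 5.0% |
| 0.1 | 5.7% | 6.1% | 6.3% |
| 0.2 | 7.9% | 9.5% | 10.4% |
| 0.3 | 11.6% | 15.2% | 17.5% |
| 0.5 | 23.9% | 33.8% | 39.7% |

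At 0.1 SD the effect is small. It becomes serious only for shifts that nothing in the protocol shows to be likely.

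**The case against.** The strongest reply is that the protocol promises blinding to treatment allocation and nothing more, so it contradicts nothing. That stands: this is a gap in bias control, not an inconsistency. It may also be said that coding before signal processing belongs in a data-handling plan. But section 12.2.3 does fix a coding scheme, and fixes it too narrowly for one of the stated main objectives.

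A reader might go further and infer that the project leader personally derives the outcomes and makes subjective choices, such as correcting marker tracks, judging when damping ends, or matching clicks to head positions. The documents do not support this:
- No section names who computes the UCM or repositioning values, or who measures the healthy participants. Section 12.1.1 says only that the project leader and an assistant transfer the calculated values.
- Section 9.2.2 has software track the markers, and no manual correction is mentioned. The accuracy of about 3 mm in section 6.1 is a limit of the device, not operator judgement.
- The end of damping is described as the point where recording stops, which masked processing cannot reach.
- Clicks are made by the participant and time-stamped.
- The use of a five-trial mean, a cited mathematical method for UCM, and sensors for centre of pressure and sway narrows the room for discretion further. Raw data are kept, so derivation can be repeated.

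One opening remains in the text. Section 12.2.4 flags values that look out of range, for example against the rest of the group. If that group means patients or healthy participants, the check depends on status.

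It is also fair that hypothesis 2 is non-directional, so no lean in a particular direction is obvious for it. Hypothesis 3 does expect reduced acuity in patients. Finally, the mismatch between 20 IDs and up to 30 patients comes from the differing sample sizes in the synopsis and section 11.2. It needs correcting, but adds no weight to the point about patient status.

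**Conclusion.** The point holds as a gap. The only coding step masks treatment arm for 20 patient IDs, and nothing masks patient or healthy status when the data for hypotheses 2 and 3 are derived and analysed. The analyst has ready means of knowing status. That the project leader runs the cross-sectional tests is read from sections 11.4.2 and 12.2.3; the gap is the same whoever computes the values, since nobody is masked.

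The size of any bias is unknown. The range of about 6% to 34% for 20 against 20 rests wholly on assumed shifts of 0.1 to 0.5 SD. It should not be read as an estimate of this study's false-positive rate. The primary outcomes, self-reported pain and function compared between arms, are not affected, and section 4.3 treats the healthy comparison as secondary although the synopsis calls it a main objective. This is a worthwhile low-cost improvement, not a fault that undermines the trial.

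**What to change.** Extend section 12.2.3 as follows.
- The technical assistant assigns every baseline record, patient and healthy, a neutral random code from one common list with no suffix that reveals status. This happens before the UCM, sway and head-repositioning values are computed from the stored coordinates and, where feasible, before marker tracking. Adding healthy IDs to the existing end-of-study recoding would not be enough.
- VAS and ODI scores are not attached to the coded records.
- Derived values and exclusions are frozen before the patient/healthy key is released. Range checks at this stage use all coded records together.
- The group comparison is run under neutral labels.
- The ID range is widened to cover all participants, once the synopsis and section 11.2 agree on the numbers. The range 87300 to 87390 holds 91 values, enough for the maximum of 50.
- The section states who computes the derived values.

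The assistant and the code range already exist, and no visit, treatment or sample size changes. The cost is that baseline records must be processed in mixed batches, so cross-sectional results come later. Masking will also be incomplete for anyone who recognises a participant on video, which is why coding at the coordinate stage is the minimum and coding before tracking is the addition where it can be done.

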#### **12.2.4 Electronic and central data validation**

Electronic data is verified by cross-checking of entered data by other members of the research group. Each file and case report form can only be saved when all relevant fields are filled in and analysis completed. A warning will appear when data is missing or data seems out range or impossible (e.g compared to the rest of the group or larger than maximum, etc.).

### **12.3 Monitoring**

The source data and documents will made accessible to monitors and questions are answered during monitoring. Monitoring will be organised internally by members of the research group who will cross-check case report forms and control file structures, folder contents and informed consent.

### **12.4 Audits and Inspections**

No additional auditing is intended for the study. Study documentation and the source data/documents are accessible to auditors and inspectors from local authorities, e.g. from the ethical committee. Questions are answered during inspections. All involved parties must keep the participant data strictly confidential.

### **12.5 Confidentiality, Data Protection**

Direct access to source documents will be permitted for purposes of monitoring (12.3), audits and inspections (12.4) (ICHE6, 6.10). For external audits, monitoring events, and inspections authorised personnel (ethics committee, CTI representatives) will have direct access to all study data. Patient data will be treated as strictly confidential and all documents will remain in the secured and locked office of the trial centre.

### **12.6 Storage of biological material and related health data**

Not applicable.

### **13. PUBLICATION AND DISSEMINATION POLICY**

The project shall eventually result in three to four publications including the findings of the cross-sectional study, a retest analysis and the RCT. Publication of a technical paper on the methodologies will be considered. It is intended to publish in open access journals relevant to the field. Authorship has been negotiated within the steering committee.

## **14. FUNDING AND SUPPORT**

### **14.1 Funding**

No funding. The project is part of the PL's Ph.D. which is financed by the sponsor-investigator. Personal costs of the PL, the therapists etc. are covered by the sponsor-investigator.

### **14.2 Other Support**

The measurement devices are provided by the ETH Zurich, Institute for Human Movement Science.

## **15. INSURANCE**

Insurance will be provided by the Sponsor-Investigator. A copy of the certificate is filed in each investigator site file and the trial master file (National Suisse, policy number 40.025.077)

